Low-income countries like Uganda suffer from shortages and an unequal distribution of trained health care providers. Almost two thirds of all physicians work in the urban regions, which serve less than one third of the population [20]. While the Ministry of Health (MOH) policy in Uganda allows both physicians and midwives to treat women with first-trimester incomplete abortions, it restricts management of second-trimester incomplete abortion to physicians [19]. The standard treatment for bleeding following an abortion in the first trimester is either misoprostol or manual vacuum aspiration, while sharp curretage by a doctor is done for women in the second trimester. The need for a surgical intervention in a setting where there is a scarcity of trained providers, sterile equipment and poor access to high-level centers limits women’s access to safe PAC, especially in remote areas. Observations in clinical practice show that the number of incomplete abortions in the second trimester are at least as high as in the first trimester in Uganda.

Evidence is compelling that the prostaglandin E1 analogue misoprostol is effective medication for first-trimester incomplete abortions [8, 22], and that there is no difference whether provided by physicians or midwives [8, 23, 24]. The choice of an equivalence trial design is to provide evidence that use of misoprostol for PAC in the second trimester when administered by physicians or midwives is equally safe, effective and acceptable. In view of the severe shortage of medical staff in rural areas and importance of task sharing to improve productivity and efficiency within a health system [21, 25, 26], the overall aim of the study is to compare the safety, effectiveness and acceptability outcomes of treatment for incomplete abortion using misoprostol when provided by midwives versus physicians in Uganda.

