### Outcomes

The primary outcome is complete abortion requiring no surgical intervention within 24 h of initiating treatment. A 24-h timeframe was chosen for clinical relevance given that the participants will be monitored at the health facility. Clinical assessment for the primary outcome includes physical and pelvic examination with attainment of a complete abortion based on cessation of uterine cramps and vaginal bleeding and a closed cervical os. An ultrasound scan is not used to diagnose a complete abortion, given its low predicting value to indicate the need of additional surgical intervention. Ultrasound scan measurement of endometrial thickness as an indicator of a complete abortion actually biases toward increased surgical interventions without significantly improving patient outcomes [31].

Secondary outcomes are assessed at the 2-week follow-up visit and include: excessive vaginal bleeding, defined as soaking more than three pads in an hour; abdominal pain, defined as discomfort experienced in the lower abdomen and intensity measured using a visual analogue scale with a minimum score of 0 representing no pain and a maximum score of 10 representing most pain; unscheduled visits, defined as participants presenting at the study site when not expected, need for additional medical treatment and experience of misoprostol side effects; sepsis, defined as presence of fever with temperature greater than 38 °C, pus or offensive vaginal discharge; time from induction (first dose of misoprostol) to completion and total dose of misoprostol given; women’s acceptability of the PAC provider with acceptability defined as positive reporting of treatment experience, recommendation of method to a friend or reuse of same method; and contraceptive uptake and discontinuation over a period of 1 year.

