### Statistical methods

Statistical analysis will be done using Stata version 13. All analyses will be by intention-to-treat (ITT) supplemented by per-protocol analysis. Background characteristics for the two study groups will be described. Categorical data will be presented as proportions and continuous data as means and standard deviations. To determine the differences in background characteristics, chi-square tests will be used for categorical data and Student *t* tests for continuous data. Analysis of the primary outcome between groups will be done using risk difference with 95% confidence intervals and equivalence established if it lies between the predefined range of − 5% and + 5%. *P* ≤ 0.05 will be considered statistically significant. Chi-square tests will be used for comparison of outcomes and Student’s *t* tests used to compare mean values. Comparisons of side effects will be carried out using Fisher’s exact tests.

We will use a generalized linear mixed-effects model with the provider as a fixed effect and the health care facility as a random effect. This will allow us, to some extent, to take into account differences in performance between the sites. Time to completion of abortion will be computed and analyzed using standard survival analysis techniques. Participants will be censored at the time that the main outcome, a complete abortion, is documented or at 24 h if no complete abortion is achieved. Time in this study will be computed in hours. Median times to completion will be derived from Kaplan–Meier estimates of the survival function and the groups will be compared using the log-rank test. Further analysis will be carried out using a Cox proportional hazards model, which establishes factors associated with time to complete abortion in a multivariable model.

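### Safety and acceptability are to be shown equal, but are compared only by difference tests at P ≤ 0.05 with no margin

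*Protocol article*

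**What the plan says.** The Background section gives the purpose of the equivalence design: to provide evidence that misoprostol in the second trimester "when administered by physicians or midwives is equally safe, effective and acceptable". That is a claim on three fronts. The Data monitoring section adds that safety is among the trial's main questions.

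Under Outcomes, effectiveness is the primary endpoint: "The primary outcome is complete abortion requiring no surgical intervention within 24 h of initiating treatment". Excessive bleeding, pain, unscheduled visits, side effects, sepsis and acceptability of the provider are secondary outcomes, and none has a margin.

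Under Statistical methods, the primary outcome has a proper equivalence rule: "Analysis of the primary outcome between groups will be done using risk difference with 95% confidence intervals and equivalence established if it lies between" −5% and +5%. The same paragraph then sets the P ≤ 0.05 threshold and continues: "Chi-square tests will be used for comparison of outcomes", with Student's t tests for means. It adds: "Comparisons of side effects will be carried out using Fisher’s exact tests". The chi-square sentence does not say whether it includes or excludes the primary outcome.

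**The concern.** The aim and the analysis do not match for two of the three claims. A chi-square, t or Fisher test takes no difference as its null hypothesis. P ≤ 0.05 is evidence of a difference; P > 0.05 says only that none was demonstrated, and when events are rare that is the likely result even if the arms truly differ. Nothing in the planned comparison of safety or acceptability can deliver a finding of equality.

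The article intends its results to inform policy on who may treat these women, which is currently restricted to physicians. If the safety table shows only non-significant P values, readers may take them as support for the Background's wording although the tests do not provide it.

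There is also a small ambiguity. Because the chi-square sentence is unrestricted and follows the ±5-point rule closely, the primary outcome could be reported with two results that answer different questions, and the text does not say which one governs.

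**Working it through.** **Inputs from the protocol article (Sample size; Statistical methods).** Success 90% in both arms, δ = 5 points, 80% power, two-sided 95% CI, 566 per arm, 5% loss, 1192 in total, significance at P ≤ 0.05.

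**Inputs that are assumptions.** The article gives no expected rates for harms or acceptability. The rates below are illustrative.

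**1. The plan's own figure.** n = 2 × 0.9 × 0.1 × (1.960 + 0.842)² / 0.05² = 565.1, rounded up to 566 per arm. 1132 / 0.95 = 1191.6, rounded up to 1192. Both stated figures are reproduced, so 566 per arm is used below. Whether this formula suits a two-sided equivalence rule is a separate question. The calculation concerns the primary outcome only; no secondary outcome was sized.

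**2. Chance that a real difference is non-significant by chi-square.** With n = 566, d = |p₁ − p₂| and p̄ the mean rate:

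- SE₀ = √(2p̄(1 − p̄)/n)
- SE₁ = √([p₁(1 − p₁) + p₂(1 − p₂)]/n)
- power = Φ((d − 1.96·SE₀)/SE₁)

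For 1% against 2%: SE₀ = 0.00723 and SE₁ = 0.00722, so power = Φ((0.0100 − 0.0142)/0.00722) = Φ(−0.576) = 0.282. The chance of P > 0.05 is 0.718.

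The Fisher figures come from summing the exact binomial probabilities of all tables with P ≤ 0.05 (power 0.205 and 0.448).

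| Assumed true rates | Non-significant, chi-square | Non-significant, Fisher |
|---|---|---|
| 1% vs 2% | 72% | 80% |
| 2% vs 4% | 50% | 55% |
| 20% vs 25% | 48% | not computed |
| 50% vs 55% | 61% | not computed |

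**3. What an interval would show instead.** If 1% and 2% were observed, the 95% CI for the difference would be 1.0 ± 1.96 × 0.722, or −0.4 to +2.4 points. The reader then sees which increase in harm remains compatible with the data. A P value above 0.05 hides this.

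**4. Would the ±5-point margin serve for these outcomes?** With equal rates p in both arms, the CI half-width is 1.96 × √(2p(1 − p)/566):

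| Rate p | Half-width (points) | Chance the CI lies within ±5 |
|---|---|---|
| 2% | 1.6 | >99% |
| 5% | 2.5 | 94% |
| 10% | 3.5 | 60% |
| 20% | 4.7 | 11% |
| 30% | 5.3 | 0 |
| 50% | 5.8 | 0 |

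For a 2% harm, 5 points is 2.5 times the base rate, so passing would say little. At 30% or 50%, passing is impossible at this sample size. One margin cannot be carried over to every outcome.

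**5. The two results on the primary outcome.** Suppose 90% and 87% are observed. The test gives z = −0.03 / √(2 × 0.885 × 0.115/566) = −1.58, P about 0.11. The 95% CI is −3.0 ± 1.96 × 1.89, or −6.7 to +0.7 points. The test is non-significant, yet the stated rule correctly withholds equivalence.

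**The case against.** **Margins only for the primary outcome are usual.** Equivalence trials commonly set a margin for the primary endpoint alone and treat the rest as supportive. That stands, and it is why margins for every secondary outcome are not demanded here. It does not rescue the Background's wording, which extends the equality claim to safety and acceptability.

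**The abstract may already cover this.** Its sentence on risk differences and the ±5% range is not restricted to the primary outcome. The Statistical methods section is the more specific text and does restrict it. If the abstract's broader reading were meant, step 4 shows that a common ±5-point margin would be too lax for rare harms and unattainable for common outcomes.

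**A reader might infer that non-significance would pass as equivalence for effectiveness.** The documents do not support this. Abstract and Statistical methods tie the equivalence conclusion to the CI alone, and no sentence says that P > 0.05 will be read as equivalence for any outcome. With no true difference, about 35% of trials would have P > 0.05 and a CI reaching beyond the margin (observed difference between 1.5 and 3.5 points), but the stated rule would not declare those equivalent. The natural reading of the chi-square sentence is that it covers the remaining outcomes.

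**A reader might also infer that ITT alone decides, with crossover pulling the result toward equivalence.** The text says "All analyses will be by intention-to-treat (ITT) supplemented by per-protocol analysis", so a per-protocol analysis is planned; how the two are combined is detail that an article may leave to the SAP. No crossover rate is given. If an assumed 10% crossover shrank a true 5-point deficit to 4.5, the chance of declaring equivalence would rise only from 2.4% to 4.3%. Requiring both analyses to lie within the margin is debatable: per-protocol is not reliably conservative in an open-label trial, and a doctor performs the evacuation after failure in both arms, so a set defined by treating cadre could lose midwife-arm failures.

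**Conclusion.** The point holds for safety, side effects and acceptability. The stated tests cannot support the stated aim of equality on those outcomes, and at this sample size non-significance would be common even if a harm doubled: about 72% (chi-square) or 80% (Fisher) for 1% against 2%, and about 50% or 55% for 2% against 4%. These percentages rest on assumed event rates and 566 evaluable women per arm. The mismatch itself needs no assumption.

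The effectiveness conclusion is not at risk from this, because its CI rule is explicit. There the only defect is loose wording about where the chi-square test applies. That safety P values would be misread is a risk the plan leaves open, not something it states.

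**What to change.** 1. For each safety, side-effect and acceptability outcome, make the between-arm risk difference (or mean difference) with its 95% CI the main result, in place of the P value.
2. State that P > 0.05 is not evidence of equal safety or acceptability.
3. Confine equivalent and equally to outcomes with a prespecified margin. If margins are wanted for key safety or acceptability outcomes, set them outcome by outcome before unblinded data are seen. Otherwise limit the equivalence aim to effectiveness and describe the rest as estimated differences.
4. State that only the 95% CI against ±5 points decides equivalence on the primary outcome, and that the chi-square sentence applies to other outcomes.

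This needs no more women and leaves the primary analysis unchanged. The cost is wording, somewhat longer tables, and a narrower claim on safety and acceptability than the Background now makes.

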### Study setting

The study is implemented in the central region of Uganda, which has a higher estimated induced abortion rate compared to the national average (52 versus 39 per 1000 live deliveries) and an accompanying huge caseload of women treated for abortion complications [29]. All selected study sites are public health facilities, equipped to provide comprehensive emergency obstetric services in rural, peri-urban and urban areas. They comprise Health Centre IVs (the lowest health care level staffed with both physicians and midwives), district hospitals and a regional referral hospital, all located within 1–2 h from Kampala, the capital city of Uganda.

Health facilities identified for inclusion in the trial have an average caseload of about 90 women with incomplete second-trimester abortions per month and sufficient staff to establish a group of 138 midwives plus other nurse-midwifery cadres at certificate, diploma and degree level and 37 physicians based on mapping of facility records data for January–June 2017, done by one of the researchers [name]. Hospital-based study sites have an average (median) of 5 (6) physicians and 19 (20) midwives, whereas the Health Centre IV study sites have an average (median) of 3 (3) physicians and 13 (16) midwives. We assume that these staff will provide an adequate pool of health providers to conduct the study. The cadre of physicians consist of medical officers and obstetricians/gynecologists with 5 years of medical training and an additional 3 years postgraduate training, respectively. Nursing and midwifery preservice programs in Uganda offer certificate, diploma or degree qualifications after 18 months, 3 years and 4 years of training, respectively. Competences are most often in midwifery and nursing, and there is provision for upgrading to a higher qualification with additional training. In this trial, a midwife is defined as a health provider who has obtained midwifery training competence as part of their preservice or additional training program.

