### Sample size

The sample size has been calculated with the objective of establishing the equivalence of misoprostol treatment of incomplete abortion provided by midwives compared with physicians, in terms of the percentage of women not requiring back-up surgical treatment. PASS software version 14 was used for sample size computations for equivalence studies, at a power of 80%, two-sided CI of 95%, set actual difference *D*_1_ range of − 5% to + 5%, smallest difference of 0.001, design effect = 1 and 5% level of significance of results [32]. If a second-trimester abortion treated with misoprostol 400 μg every 6 h administered vaginally has an effectiveness of 90% at 48 h, we assume that the same dose used every 3 h sublingually for second-trimester incomplete abortion would have around 90% effectiveness at 24 h given the faster onset of action for the sublingual route [33]. If both allocation arms have the same success rates within an equivalence margin of 10%, then 566 women will be required in each arm. Considering a loss to follow-up of 5%, 1192 women will be recruited for the study. Table 1 presents the various sample size scenarios, with a δ value of 5% and power of 80% chosen based on the feasibility of accruing the sample size.

**Table 1 Tab1:** Sample size scenarios

δ (%)	Power = 80%	Power = 90%
4	884 (1768)	1183 (2366)
5	566 (1132)	757 (1514)

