## Limitations

The study is implemented at study sites with variable client caseloads due to the differing levels of health care provision. We have addressed this using blocked randomization to cater for the uneven number of participants from each site. The health care providers to whom women are randomized work closely at the clinic and within the same environment, which might affect the outcome. Health care providers’ years of working experience might differ between the two groups of midwives and doctors and by individual. Most commonly, midwives working in rural area have longer work experience than doctors. In addition, the health provider’s individual attitude and experiences of using misoprostol might further impact the outcome. All health providers at the participating health facilities will undergo standardized training to strengthen the internal validity.

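### Clinicians are nested in arm, but the plan sets the design effect to 1 and makes only facility random; if outcomes vary between clinicians, the equivalence interval will be too narrow

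*Protocol article*

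**What the plan says.** The Sample size section of the protocol article makes no allowance for clustering: "design effect = 1 and 5% level of significance of results". It assumes that treatment "would have around 90% effectiveness at 24 h" in both arms and arrives at 566 women per arm, 1192 recruited.

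Under Statistical methods, the primary analysis is a risk difference with a 95% confidence interval, with "equivalence established if it lies between the predefined range of" −5% to +5%. The next paragraph adds the only model for between-unit variation: "We will use a generalized linear mixed-effects model with the provider as a fixed effect and the health care facility as a random effect". Its stated purpose is to allow for performance differences between sites.

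Study setting reports that the facilities have "sufficient staff to establish a group of 138 midwives plus other nurse-midwifery cadres at certificate, diploma and degree level and 37 physicians". Under Procedure, the allocated provider assesses the woman, gives each dose and monitors her every 3 hours. A provider in the allocated arm diagnoses completion, and an independent assessor verifies it. Limitations says that experience may differ between individuals and that the provider's "individual attitude and experiences of using misoprostol might further impact the outcome". The remedy it offers is standardized training.

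**The concern.** The randomized comparison is between physicians and midwives, and no clinician can appear in both arms. If some clinicians tend to get better results than others, or judge completion or turn to surgery sooner, outcomes of women under the same clinician are correlated. Because clinicians are nested in arm, that variation goes straight into the variance of the arm difference.

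The model described does not pick it up. 'Provider' as a fixed effect can only mean provider type, that is, the arm: a separate fixed effect for each clinician would be collinear with arm, and the arm difference could not be estimated. Randomization is stratified by site, so each facility contributes women to both arms. A facility intercept shifts both arms together and leaves clinician-within-arm variation where it was.

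In an equivalence trial the direction matters. An interval that is too narrow fits more easily inside ±5%, so the error favours the trial's positive conclusion. Applying the result to midwives and physicians in general also requires between-clinician variation in the error term.

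**Working it through.** **Inputs.** From Sample size: 90% success in both arms, 80% power, two-sided 95% interval, design effect 1, 566 per arm, 5% loss. From Statistical methods: margin 5 points. From Study setting: 37 physicians; 138 midwives and other cadres. The ICC is not in the protocol, so I assume 0.01, 0.02 and 0.05.

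**1. Reproduce the plan's figure.** n = (1.960 + 0.842)² × (0.9×0.1 + 0.9×0.1) / 0.05² = 565.1, so 566 per arm. Recruitment: 1132 / 0.95 = 1191.6, so 1192. Both match, with no allowance for clustering. The 80% refers to one confidence limit only (a one-sided calculation), and the power figures below are on that same basis.

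**2. Illustrative caseloads.** 566/37 = 15.3 women per physician; 566/138 = 4.1 per midwife.

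**3. Design effect and standard error.** Per arm, DE = 1 + (m − 1) × ICC. With equal arms and equal success rates, the standard error grows by the square root of the mean DE. For ICC 0.02: physicians 1 + 14.3×0.02 = 1.286; midwives 1 + 3.1×0.02 = 1.062; mean 1.174; √1.174 = 1.084.

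**4. Coverage.** Actual coverage of the unadjusted interval = 2Φ(1.96/√mean DE) − 1.

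**5. False equivalence at a true 5-point difference (90% vs 85%).** The unadjusted SE is s0 = √[(0.09 + 0.1275)/566] = 0.0196. The true SE, s1, multiplies each arm's variance by its own DE. Both limits must lie inside ±5%, so the probability is Φ[(0.10 − 1.96 s0)/s1] − Φ[1.96 s0/s1]. With no clustering this is 2.4%. With clustering it depends on which arm has the 85%, hence the ranges.

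**6. Power if the interval is correctly widened.** Unadjusted SE at 90% = √(0.18/566) = 0.01783. One-sided power = Φ[0.05/(0.01783 × √mean DE) − 1.96].

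| Assumed ICC | DE physicians / midwives | SE ratio | Coverage | False equivalence | One-sided power |
|---|---|---|---|---|---|
| 0 | 1.00 / 1.00 | 1.00 | 95.0% | 2.4% | 80% |
| 0.01 | 1.14 / 1.03 | 1.04 | 94.0% | 2.8–2.9% | 76.7% |
| 0.02 | 1.29 / 1.06 | 1.08 | 93.0% | 3.2–3.4% | 73.5% |
| 0.05 | 1.71 / 1.16 | 1.20 | 89.8% | 4.4–4.9% | 64.8% |

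**7. Check by simulation.** A beta-binomial simulation (20,000 runs per setting) of the unadjusted interval gave coverage of 94.1%, 92.8% and 90.0% at equal success rates. With physicians at 90% and midwives at 85%, it gave false equivalence of 3.0%, 3.2% and 4.5%, against 2.4% without clustering. This agrees closely with the formulas.

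**8. Uneven caseloads.** With a coefficient of variation of 0.7 (an assumption), DE = 1 + [(1 + 0.7²)m − 1] × ICC. At ICC 0.05 this gives 2.09 and 1.26, an SE ratio of 1.29 and coverage of 87%.

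**The case against.** The size rests on inputs the protocol does not supply. No ICC is given, and at 0.01 the standard error is only 4% larger. The 37 and 138 are a staff pool mapped from January–June 2017 facility records, not a list of treating clinicians, and the wording of the 138 includes other nurse-midwifery cadres. So 15 and 4 women per clinician are not documented caseloads.

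Several features may lower the correlation. The regimen is fixed, training is standardized, up to five doses within 24 hours may be shared among staff, completion is diagnosed by a provider in the allocated arm rather than necessarily the same person, and a blinded assessor verifies it. All of this stands as a limit on size. None of it makes the ICC zero: verification at the end does not remove differences in earlier assessment, monitoring or the decision to move to surgery. Fewer active staff or uneven caseloads would push the other way.

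It may also be said that this is analysis-plan detail. That would hold if the article were silent, but it states both the design effect and the random-effects structure.

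A reader might further infer that the primary interval ignores clustering altogether. The text does not settle this. It does not say whether the risk difference is crude or derived from the mixed model, and an article may leave that to the analysis plan. On either reading, no clinician-level term is described.

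**Conclusion.** The concern holds conditionally. The stated design effect and model leave out a source of variation that the protocol itself names, and the omission is anti-conservative for equivalence under any positive clinician ICC. At the illustrative caseloads the effect is small at ICC 0.01 and material at 0.05, where coverage is about 90%, false equivalence is nearly doubled and the planned 80% one-sided power drops to about 65%.

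A reader might conclude that the interval is definitely too narrow, or that an equivalence finding would be invalid. The protocol does not support that: the ICC is unknown, the caseloads are illustrative, and shared care and blinded verification may keep the correlation low. The plan should be changed, but nothing here shows that the trial will reach a wrong conclusion.

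**What to change.** - Record the ID of the main treating clinician for each woman, or use it if the clinical notes already hold it. The article does not list the form fields, so this needs checking.
- Derive the risk-difference interval with a clinician-level random intercept nested in arm and facility, or with standard errors clustered by clinician and a small-sample correction because there are few physicians. At minimum, make this a prespecified sensitivity analysis on which the equivalence claim must also hold.
- State that 'provider' as a fixed effect means provider type.
- Replace the design effect of 1 in the power statement with the assumed ICC range and the resulting power. The sample size need not change.

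The cost is a slightly wider interval, lower stated power, one data field and some analysis wording. Recruitment began on 14 August 2018, so if the ID was not captured from the start, it would have to be recovered from the notes of women already enrolled. Where care was shared, assigning one main clinician is an approximation and should be described as such.

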In the case that no complete abortion has been achieved within 24 h from the time the first dose of misoprostol was administered, a doctor performs a surgical method of uterine evacuation using MVA or blunt curettage. Patients can also be discontinued from medical management and surgical management instituted if their condition worsens during treatment or on request. All participants are discharged 4 h after completing the abortion if there are no complications. Before discharge, women receive detailed information regarding abnormal symptoms (fever, foul smelling vaginal discharge, bleeding and pain), when to seek care, and contraceptive counselling and provision, and advised to return for a follow-up visit 14 days after treatment. A detailed description of the study participant timeline is provided in Fig. 2.

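### The time-to-completion rule calls every woman censored, completers included: the exit times are right, but completion must be named as the event

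*Protocol article*

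**What the plan says.** The Outcomes section of the protocol article lists among the secondary outcomes "time from induction (first dose of misoprostol) to completion and total dose of misoprostol given". Statistical methods then sets out the analysis: "Time to completion of abortion will be computed and analyzed using standard survival analysis techniques". The status rule follows, in a single sentence with two limbs. The first is "Participants will be censored at the time that the main outcome, a complete abortion, is documented". The second is "or at 24 h if no complete abortion is achieved".

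The same paragraph names three analyses of this time. The first two come together: "Median times to completion will be derived from Kaplan–Meier estimates of the survival function and the groups will be compared using the log-rank test". The third is a "Cox proportional hazards model, which establishes factors associated with time to complete abortion in a multivariable model".

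Two other places bear on the rule. Outcomes defines the primary outcome as a complete abortion within 24 h of starting treatment for which no surgery was needed. The Procedure section allows medical treatment to be stopped early, with "surgical management instituted if their condition worsens during treatment or on request".

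**The concern.** In a time-to-event analysis each woman needs an exit time and a status, which is either event or censored. For time to completion, the documented completion is the event. The rule gives it the status censored, gives the same status to everyone else at 24 h, and says nowhere what an event is. This is a rule stated wrongly, not a detail left to an analysis plan that is not shown.

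What is at stake is one secondary outcome. A programmer who followed the sentence to the letter would have nothing to analyse. A programmer who corrected it silently would be using a coding that the published plan does not contain.

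**Working it through.** **Figures in the plan.** The article gives no event count or median for this analysis, so there is none to reproduce. The bases come from Sample size: 566 per arm, so 2 × 566 = 1132, and with 5% loss 1132 / 0.95 = 1191.6, rounded up to 1192, as stated. The assumed success at 24 h is 90%.

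**Step 1: the rule as written.** Completers are censored at completion and non-completers at 24 h. The two groups make up the whole trial, so events = 0.

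- Kaplan–Meier: S(t) = ∏(1 − d/n) over event times, with d events among n at risk. With no event times S(t) = 1 throughout, never reaches 0.5, and the median is undefined.
- Log-rank: the statistic is (ΣO − ΣE)² / ΣV, summed over event times. With none, both numerator and denominator are 0.
- Cox: the partial likelihood is a product over events. With none it has no terms and carries no information on any coefficient.

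**Step 2: completion as the event, the rest censored at 24 h.**

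| Base | Events (90%) | Censored (10%) |
|---|---|---|
| 1192 recruited | 0.90 × 1192 = 1072.8, about 1073 | 119.2, about 119 |
| 1132 after the loss allowance | 0.90 × 1132 = 1018.8, about 1019 | 113.2, about 113 |

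The base of 1192 fits better, because the analysis is by intention to treat and the main outcome is assessed before discharge.

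**Step 3: a check on simulated data.** Times were drawn for 1192 women with the same distribution in both arms. They were assumed exponential with 90% complete by 24 h: rate = −ln(0.1)/24 = 0.0959 per hour, median = ln(2)/0.0959 = 7.2 h. The shape is an assumption, so the medians only illustrate.

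- Coded as written: 0 events, both medians undefined, the log-rank computation stopped on a singular matrix, and the Cox fit failed.
- Coded with completion as the event: 1070 events, medians of 6.9 h and 7.7 h, and the log-rank test and Cox model both ran.

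The exit times were identical in the two runs. Only the status differed.

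**Step 4: surgery before 24 h.** The first limb refers to the main outcome, and Outcomes defines the primary outcome as needing no surgery. A woman evacuated at, say, 6 h therefore cannot have the main outcome, even if bleeding and cramps later stop and the os closes. She falls under the second limb, with exit at 24 h and no event.

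**The case against.** The strongest reply is that nobody would analyse the trial this way. The paragraph calls the endpoint time to completion, plans "Median times to completion will be derived from" Kaplan–Meier estimates, and models time to complete abortion. Completion is the only event that these phrases allow. On this reading the sentence says when each woman's clock stops, and says so correctly. A statistician is to be involved in the analysis, and an all-censored dataset would fail at once. This stands as an account of what was meant, and it limits the weight of the point. It does not make the sentence correct: the status is still stated wrongly, and nothing elsewhere in the article corrects it.

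A reader might infer two stronger things. The first is that the planned analyses will yield no result. That follows only from a literal coding that the adjacent sentences contradict.

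The second is that the rule lets early surgery bias the comparison, with the arm that operates sooner appearing faster. That would require surgical evacuations to be counted as completions or censored at the time of surgery, and the plan states neither. The definition under Outcomes points the other way, and the article gives no rate of early surgery and no difference between arms. What remains is a matter of clarity: the rule speaks both of the main outcome and, more loosely, of a complete abortion, so an explicit link to the definition is worth adding.

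**Conclusion.** The point holds as a mislabelled status in the analysis of one secondary outcome. Read literally the rule gives 0 events, against about 1073 of 1192 women (about 1019 of 1132) once completion is the event. The counts rest on the plan's own 90% success assumption; the finding of 0 events needs no assumption beyond the wording. The most likely explanation is a slip in which censored stands for end of follow-up.

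The primary risk difference, the equivalence decision and the sample size do not depend on this sentence, and no bias is shown, from early surgery or otherwise. I rate it a minor-to-moderate correction, not one on which the trial's conclusion turns.

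**What to change.** Replace the sentence on censoring under Statistical methods with wording such as:

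> The event is the main outcome as defined under Outcomes, at its documented time. Women who have not had it by 24 h, including those who had surgical evacuation earlier, are not events and are censored at 24 h.

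The first sentence corrects the status. The clause on earlier evacuation only makes explicit what the Outcomes definition already implies. It concerns analysis coding and changes no clinical rule.

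The cost is this change of text, best made before the analysis. No new data are needed, because Procedure already has the provider record the time of completion.
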